## Abstract

**Background:**

In critically ill patients admitted to the intensive care unit (ICU), early nutritional therapy and mobilization rehabilitation are considered important interventions; however, when applied independently, neither approach has consistently demonstrated clear benefits in improving clinical outcomes. To date, no study has specifically examined the potential synergistic effects of combining high-protein nutrition with early mobilization. Therefore, this trial aims to investigate whether combining these interventions can promote physical and functional recovery after ICU discharge.

**Methods:**

This single-center, prospective, participant- and assessor-blinded randomized controlled trial with a planned sample size of 90 critically ill patients will be conducted in the ICU of a tertiary emergency care facility. Mechanically ventilated adult patients in the ICU will be eligible. Participants will be randomly assigned to either a “usual-protein group” (1.2 g/kg/day) or a “high-protein group” (1.8 g/kg/day). In both groups, early mobilization will be delivered according to a standardized protocol using a mobile patient lift, enabling patients to achieve standing or higher-level activities early in the ICU course. The primary outcome will be the motor score of the Functional Independence Measure (FIM) at hospital discharge. Secondary outcomes will include the Cognitive subscale of the Functional Independence Measure, Brief Pain Inventory score, ICU length of stay, hospital length of stay, and discharge disposition. Written informed consent will be obtained from participants or their legally authorized representatives prior to enrollment.

**Discussion:**

This trial will be the first to evaluate the potential synergistic effects of high-protein nutrition and standardized early high-intensity mobilization in ICU patients. By focusing on protein dose as the sole intervention variable and using a mobile patient lift to ensure uniform mobilization intensity, the study is designed to provide robust evidence regarding the role of high-protein nutrition during intensive rehabilitation. This trial is conducted in accordance with the SPIRIT guidelines. The findings are expected to inform future multicenter trials and contribute to the development of clinically relevant strategies to improve post-ICU functional recovery.

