Emerging evidence suggesting a U-shaped relationship between protein intake and outcomes should be interpreted in the context of limited or heterogeneous mechanical loading in prior trials. In most large RCTs evaluating higher protein provision, mobilization intensity was low, poorly standardized, or not systematically reported. Under such conditions, excess amino acid availability may not be effectively utilized for muscle protein synthesis and could instead contribute to metabolic burden. Therefore, we hypothesize that the optimal protein dose is not fixed, but rather depends on the presence of sufficient mechanical stimuli. In this framework, higher protein provision may be beneficial only when adequate resistance-type mobilization is ensured.

However, in real-world practice, achieving high-intensity mobilization, particularly out-of-bed activities such as standing and walking, remains challenging owing to personnel and equipment constraints [20, 21]. Such variability may obscure the clinical benefits of nutritional interventions. To address this issue, we previously reported that the use of a mobile patient lift (MPL, Golvo® 9000 lowBase (Hillrom BV, Amsterdam, The Netherlands)) enables mechanically ventilated patients to achieve early standing and improves functional independence during their ICU stay [22]. Based on these considerations, we hypothesize that higher protein intake enhances functional recovery only when combined with standardized high-intensity mobilization, whereas protein supplementation alone may be insufficient to improve functional outcomes in critically ill patients. Building on this, the present study aims to establish a realistic and standardized approach to high-intensity mobilization using an MPL for all eligible patients, and to evaluate the clinical significance of high-protein nutrition in this context through a single-center, participant- and assessor-blinded, randomized controlled trial. The primary objective of this randomized controlled trial is to evaluate whether higher protein intake improves functional recovery in ICU patients receiving enteral nutrition when combined with standardized early high-intensity mobilization.

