### Interventions

The intervention in this study will not involve differences in the intensity or frequency of rehabilitation; the focus will be on modifying protein intake between the two groups. In the control group, nutritional support will target the lower limit of protein intake recommended in current guidelines (1.2 g/kg/day) [9, 10]. In contrast, participants in the intervention group will receive a higher protein intake of 1.8 g/kg/day. As described previously, both caloric and protein intake will be adjusted to remain within 100–110% of the prescribed targets. Although European Society for Clinical Nutrition and Metabolism guidelines suggest higher protein targets for selected populations, such as trauma or obese patients [9], the present trial is not designed to individualize protein prescription based on diagnostic subgroups, but rather to evaluate the effect of two predefined protein targets under standardized mobilization conditions. Randomization is expected to distribute such patient characteristics evenly between groups.

The core intervention period will continue from Day 3, when protocolized protein delivery is initiated, until ICU discharge, death, or the initiation of oral intake, whichever occurs first, for a maximum of 28 days from randomization. During this period, standardized high-intensity mobilization will be provided as part of routine ICU care to all eligible patients.

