## Discussion

This study is designed to evaluate whether high-protein nutrition contributes to improved physical function in critically ill patients, specifically focusing on a cohort undergoing earlier and more intensive mobilization than is typical in conventional practice. The findings are expected to provide valuable evidence on the potential synergistic effects of high-protein nutrition and rehabilitation.

Previous studies have shown that both high-protein nutrition and early mobilization, when implemented separately, offer only modest benefits. Moreover, several trials have investigated the combined use of nutrition and exercise therapy. For example, RCTs conducted by Wu et al. [32] and de Azevedo et al. [33] examined the effect of combined interventions. In the study by Wu et al. [32], a four-arm comparison was performed to assess resistance training with or without beta-hydroxy-beta-methylbutyrate (HMB) supplementation. Although the intervention improved certain aspects of physical function, the nutritional component was based on HMB rather than dietary protein intake set at a level that could be classified as high-protein nutrition.

In the study by de Azevedo et al. [33], high-protein nutrition (2.0–2.2 g/kg/day) was combined with exercise using a cycle ergometer. While the protein intake satisfied the criteria for high-protein nutrition, the simultaneous intensification of both exercise and diet made it difficult to isolate the independent contribution of each intervention. Moreover, the cycle ergometer primarily provides aerobic exercise, raising concerns regarding variability in exercise intensity and limited muscle loading.

In contrast, the present study will employ an MPL to deliver standardized, high-intensity mobilization (defined as standing or higher) for all participants, thereby ensuring consistency in exercise intensity and implementation. By using protein dose as the sole intervention variable, this study will enable a more rigorous evaluation of the direct effects of protein intake on physical function. Furthermore, MPL can be safely applied even in patients with mild consciousness disturbances or muscle weakness, enhancing both the standardization of rehabilitation and the inclusiveness of the intervention cohort.

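### The trial claims to evaluate synergy between protein and mobilisation, but both arms receive the same mobilisation, so no randomised interaction can be estimated

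*Protocol article*

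**What the plan says.** The protocol article makes the synergy claim in several places.

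- **Abstract, Discussion:** "This trial will be the first to evaluate the potential synergistic effects of high-protein nutrition and standardized early high-intensity mobilization in ICU patients".
- **Abstract, Background:** the gap to be filled is that synergy between the two interventions has not been studied, and the trial is presented as the answer to that gap.
- **Background (main text):** "we hypothesize that higher protein intake enhances functional recovery only when combined with standardized high-intensity mobilization, whereas protein supplementation alone may be insufficient" to improve function.
- **Discussion (main text):** "The findings are expected to provide valuable evidence on the potential synergistic effects of high-protein nutrition and rehabilitation".

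The design is described as follows.

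- **Abstract, Methods:** two arms, with protein targets of 1.2 and 1.8 g/kg/day. On mobilisation: "In both groups, early mobilization will be delivered according to a standardized protocol using a mobile patient lift".
- **Interventions:** "The intervention in this study will not involve differences in the intensity or frequency of rehabilitation". The Discussion likewise names protein dose as the only variable that is manipulated.
- **Statistical analyses:** the primary analysis is a two-group intention-to-treat comparison.

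The sentence labelled as the primary objective, at the end of the Background, is narrower than the claim. The trial is to "evaluate whether higher protein intake improves functional recovery in ICU patients receiving enteral nutrition when combined with standardized early high-intensity mobilization".

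**The concern.** Synergy, and benefit that arises only in combination, are both statements about a difference between two protein effects: one with high-intensity mobilisation and one without it. This trial observes only the first.

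What is at stake is the conclusion. The Background explains earlier neutral protein trials by insufficient mechanical loading. If this trial is positive, the abstract and Discussion invite readers to take that as support for the explanation, although a protein effect that does not depend on mobilisation would produce the same data. If it is neutral, readers may conclude that there is no synergy, which the data could not show either. The abstract expects the findings to inform multicentre trials, so a misreading would carry forward.

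**Working it through.** **1. What the stated sample size covers.** Inputs from Sample size estimation: difference 17 points on FIM motor score, SD 20, two-sided alpha 0.05, and 0.95, which is printed as beta but reproduces the result only as power.

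- Normal approximation: n per group = 2 × [20 × (1.960 + 1.645) / 17]² = 2 × 17.99 = 35.98, so 36.
- Two-sample t-test: 36.96, so 37 per group and 74 in total, as stated.
- Dropout: 74 / 0.85 = 87.1, so 88. The stated 90 is slightly above this.

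The figure reproduces. It is a calculation for one contrast, high versus usual protein, and contains no interaction.

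**2. What the design identifies.** Write M for the mobilisation programme and define

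- D₁ = mean FIM motor (1.8, with M) − mean FIM motor (1.2, with M)
- D₀ = mean FIM motor (1.8, without M) − mean FIM motor (1.2, without M)
- Interaction (synergy) = D₁ − D₀

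| | 1.2 g/kg/day | 1.8 g/kg/day |
|---|---|---|
| With M | 45 randomised | 45 randomised |
| Without M | 0 | 0 |

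(90 patients allocated 1:1 gives 45 per arm.) D₁ is estimable and D₀ is not. Equivalently, a design matrix with columns for intercept, protein, mobilisation and protein × mobilisation, with mobilisation constant, has rank 2 of 4. The product column is identical to the protein column. More patients do not change this.

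**3. What each result could mean.** The D₀ values below are assumptions for illustration; the article gives none.

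| Observed D₁ | Assumed D₀ | Interaction |
|---|---|---|
| 17 | 0 | 17 (protein works only with M) |
| 17 | 17 | 0 (protein works regardless of M) |
| 0 | 0 | 0 (no effect either way) |
| 0 | −8.5 | 8.5 (M offsets a harm of protein alone) |

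The first two rows give identical trial data, and so do the last two. The last row is not far-fetched: the Background itself says that stand-alone high protein may be harmful in some settings.

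**4. Whether the planned mobilisation analyses fill the gap.** The ANCOVA takes the duration of mobilisation as a covariate, and Subgroup analysis splits by it. That duration arises after randomisation, is not itself randomised, and varies only among patients who are all assigned the programme. It may be influenced by recovery and by the allocated protein. It could give an observational estimate of effect modification at most, and it never reaches the cells without M.

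**5. Scale of a trial that could test synergy.** For a 2 × 2 factorial with SD 20 and two-sided alpha 0.05, n per cell = 4 × [20 × (1.960 + z_power) / interaction]². The interaction sizes are assumptions.

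| Interaction | Power | Per cell | Total |
|---|---|---|---|
| 17 | 95% | 72 | 288 |
| 17 | 80% | 44 | 176 |
| 8.5 | 95% | 288 | 1,152 |
| 8.5 | 80% | 174 | 696 |

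Spreading 90 patients over four cells (22.5 each) gives a standard error of √(4 × 400 / 22.5) = 8.43, hence power of about 52% for 17 points and 17% for 8.5 points.

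**The case against.** The strongest reply is that the working parts of the plan already ask the narrower question. The labelled primary objective is the protein effect under standardised mobilisation, the Interventions section describes the comparison in the same terms, and the sample size and primary analysis match it. No interaction test is planned or powered. The synergy wording is softened by *potential*, and the Background sentence is marked as a hypothesis. No conclusion about synergy is fixed in advance. The mobilisation-duration analyses are offered as exploratory and not as a test of synergy. Delivered mobilisation will also vary in practice.

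Much of this stands. The primary comparison is coherent. The first half of the hypothesis, that more protein helps when mobilisation is provided, is tested directly, and a null result would count against it. Because delivered mobilisation varies, the exact statement is that no *randomised* interaction can be estimated.

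It does not rescue the claim. *Potential* qualifies whether synergy exists; the abstract still says without qualification that the trial will evaluate it. A primary objective that the design can answer, beside a headline aim that it cannot, makes the article inconsistent with itself. Earlier trials cannot stand in for the empty cells: no comparison with them is planned, and the Background describes mobilisation in most of them as low, poorly standardised or not systematically reported. Nor can a separate analysis plan supply cells that were never randomised.

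**Conclusion.** The claim to evaluate synergy is wrong as written. The randomised design estimates one simple effect, 1.8 versus 1.2 g/kg/day given mobilisation. The protein-by-mobilisation interaction is not identified at any sample size, because 0 of 90 patients are randomised to either protein target without the programme. The part of the hypothesis that says protein works only in combination is therefore untestable here.

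This rests on the article's own description of the arms and needs no assumed effect size; the factorial sample sizes are illustrative only. The fault lies in the aim and the permitted conclusion. The primary comparison and its sample size are unaffected, so this is something that should be corrected, not a defect that invalidates the trial.

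**What to change.** Keep the design and change the wording.

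- In the abstract (Background and Discussion), the hypothesis and the main Discussion, state the question as: *whether a protein target of 1.8 rather than 1.2 g/kg/day improves FIM motor score at hospital discharge in patients who all receive standardised early mobilisation*.
- Remove synergy, and benefit only in combination, as things the trial tests. They can stay in the Background as biological rationale, labelled as such.
- Add to the limitations that the protein effect without the programme is not observed, that neither a positive nor a null result speaks to synergy, and that analyses by mobilisation duration are observational.
- State that testing synergy would need a factorial trial in which mobilisation is randomised as well.

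The cost is a narrower claim. Arms, N = 90, endpoint and primary analysis do not change, and the primary objective sentence already fits. Trial status reports no participants enrolled at submission, so the wording can be settled before any results are known.

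By contrast, a factorial trial for a 17-point interaction at 95% power would need 288 / 0.85 = 339 patients after 15% dropout. At the article's rate of 90 in about 20 months (4.5 a month), that is about 75 months.

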**Trial registration:**

University Hospital Medical Information Network Clinical Trials Registry (UMIN-CTR), UMIN000059233. Registered on September 29, 2025. https://center6.umin.ac.jp/cgi-open-bin/ctr_e/ctr_his_list.cgi?recptno=R000067751.

**Supplementary Information:**

The online version contains supplementary material available at 10.1186/s13063-026-09584-9.

## Background

In the intensive care unit (ICU), comprehensive care that addresses not only acute management but also long-term functional outcomes has become increasingly important [1–3]. Among the strategies proposed, adequate protein delivery and early mobilization are widely recognized as key interventions aimed at mitigating muscle loss [4, 5] and preventing the development of post-intensive care syndrome [6–8]. International guidelines recommend protein intake of 1.2–2.0 g/kg/day to promote muscle protein synthesis and improve functional outcomes [9, 10].

Malnutrition is highly prevalent among critically ill patients. A systematic review that used validated nutritional assessment tools reported that 38–78% of patients were malnourished at or shortly after ICU admission [11]. Importantly, malnutrition diagnosed by formal nutritional assessment was independently associated with adverse clinical outcomes, including increased ICU length of stay, ICU readmission, infectious complications, and hospital mortality, even after adjustment for illness severity and comorbidities. These findings underscore malnutrition as a clinically meaningful and independent risk factor for poor outcomes in the ICU and highlight the urgency of optimizing nutritional strategies in this population.

However, accumulating evidence indicates that higher protein intake does not uniformly translate into better clinical outcomes. Recent randomized controlled trials (RCTs) have reported that protein delivery exceeding 1.2 g/kg/day, when administered as a stand-alone intervention, does not significantly improve patient-centered outcomes [12] and may even be harmful in certain clinical contexts [5, 13]. Observational studies further suggest that the relationship between protein intake and outcomes such as mortality may follow a U-shaped pattern, with moderate protein targets being associated with more favorable short-term outcomes, while higher targets confer no additional benefit [14, 15]. Consistent with these findings, an updated meta-analysis has reported heterogeneous effects of higher protein intake on clinical outcomes, highlighting the limitations of protein supplementation as a stand-alone intervention [5]. Similarly, although various early mobilization strategies, including in-bed exercise and out-of-bed activities, have been proposed [6, 8], large-scale RCTs have not demonstrated consistent improvements in functional outcomes when mobilization is implemented without sufficient standardization or intensity [16].

Thus, while both high-protein nutrition and early mobilization are recognized as important ICU interventions, their effects may be limited when applied independently. Evidence from basic research suggests that muscle protein synthesis is most effectively promoted by the synergistic interaction of nutritional and mechanical stimuli [17–19]. This finding implies that the benefits of high-protein nutrition can only be realized when sufficient mobilization intensity is ensured. At the molecular level, resistance-type muscle contraction activates anabolic signaling pathways, particularly the mammalian target of rapamycin complex 1 (mTORC1), which plays a central role in regulating muscle protein synthesis. Essential amino acids, especially leucine, act as key upstream regulators of mTORC1 signaling; however, nutrient-driven stimulation of muscle protein synthesis is transient when provided alone [19]. Mechanical loading through exercise prolongs and amplifies amino acid-induced anabolic signaling, providing a biological rationale for expecting synergistic effects between high-protein intake and high-intensity mobilization.

Emerging evidence suggesting a U-shaped relationship between protein intake and outcomes should be interpreted in the context of limited or heterogeneous mechanical loading in prior trials. In most large RCTs evaluating higher protein provision, mobilization intensity was low, poorly standardized, or not systematically reported. Under such conditions, excess amino acid availability may not be effectively utilized for muscle protein synthesis and could instead contribute to metabolic burden. Therefore, we hypothesize that the optimal protein dose is not fixed, but rather depends on the presence of sufficient mechanical stimuli. In this framework, higher protein provision may be beneficial only when adequate resistance-type mobilization is ensured.

However, in real-world practice, achieving high-intensity mobilization, particularly out-of-bed activities such as standing and walking, remains challenging owing to personnel and equipment constraints [20, 21]. Such variability may obscure the clinical benefits of nutritional interventions. To address this issue, we previously reported that the use of a mobile patient lift (MPL, Golvo® 9000 lowBase (Hillrom BV, Amsterdam, The Netherlands)) enables mechanically ventilated patients to achieve early standing and improves functional independence during their ICU stay [22]. Based on these considerations, we hypothesize that higher protein intake enhances functional recovery only when combined with standardized high-intensity mobilization, whereas protein supplementation alone may be insufficient to improve functional outcomes in critically ill patients. Building on this, the present study aims to establish a realistic and standardized approach to high-intensity mobilization using an MPL for all eligible patients, and to evaluate the clinical significance of high-protein nutrition in this context through a single-center, participant- and assessor-blinded, randomized controlled trial. The primary objective of this randomized controlled trial is to evaluate whether higher protein intake improves functional recovery in ICU patients receiving enteral nutrition when combined with standardized early high-intensity mobilization.

## Methods

This protocol was developed in accordance with the SPIRIT guidelines.

